**Objective:**

This pilot randomized controlled trial (RCT) evaluates the preliminary efficacy and successful implementation of TACSI, a 6-session semistructured psychosocial and psychoeducational program, over a 6-month period.

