A TACSI intervention manual provided an overarching structure and guide to facilitate the coach’s intervention delivery. The semistructured nature of the program allows coaches the flexibility to tailor the intervention based on the caregiver’s needs and priorities. All topics in the manual are offered during the intervention, but the depth of exploration, if any, is determined by the caregiver. Further, tailoring and personalization of the session content and focus are emphasized by the caregiver guiding the selection of topics to discuss and deciding when to discuss them during the intervention.

**Table 2. T2:** TBI-AD/ADRD^a^ caregiver support intervention (TACSI) delivery characteristics.

Dimension	Options
Method of caregiver/coach contact	Telephone Secure video conferencing (ie, Zoom) Email Mail
Intervention materials	Coaches: Treatment manual Computer with word processing for session notes Internet access (for secure video conferencing, ie, Zoom; resource identification/use) Printer to share resources if needed Caregivers: Computer, phone, or both to access remote intervention
Delivery location	Remote delivery via: Telephone Secure video conference calls
Schedule: duration and intensity	Session types: Six weekly TACSI sessions (approximately 60 minutes each) Ad hoc consultation as needed (approximately 45 minutes) Participants could voluntarily withdraw from intervention at any time. Time needed for documentation (approximately 30 minutes post-session): Session dates Session length Number of ad hoc sessions Length of ad hoc sessions Session notes
Scripting/tailoring of intervention	Semistructured intervention based on treatment manual General guidelines and some language provided; elaboration and discussion encouraged Topics specified; coach tailoring of which topics to discuss and when, based on caregiver priorities and needs Personalization emphasized based on caregiver and care recipient background, experiences, and abilities
Sensitivity to participant characteristics	Personalization of session content/topics (see Scripting/Tailoring of Intervention) Language preferences, literacy, visual supplements/augmented communication have not been incorporated or requested by participants

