#### Surveys

Caregivers received a baseline survey collecting information on sociodemographics, context of care, and outcome measures. The baseline survey contained sociodemographic measures for both the caregiver and care recipient (date of birth, gender, racial background, marital status, education level, and household income). Context of care variables, such as geographic location, caregiver work status, health conditions, and relationship to care recipient were assessed. Additional variables included year and severity/type of TBI and AD/ADRD diagnoses with concurrent symptoms, care recipient Veteran and Medicaid status, and living arrangement.

Two follow-up surveys were administered by a research assistant blinded to participant group assignment from randomization through the end of analysis. The first follow-up (T1) was administered at 3 months post completion of the baseline survey; the second follow-up was administered 3 months after completion of the 3-month survey (T2). If a care recipient passed away during the study, modified bereavement surveys were administered at follow-up.

Three options for completing surveys were offered: online via Qualtrics, a mailed survey, or over the phone with study staff. The specific measures selected for assessment have strong psychometric properties; Table 1 displays outcome measures administered by time point and survey type. Primary outcome measures assessed perceived burden, caregiver relationship satisfaction, caregiving ideology, and caregiving mastery using the Modified Caregiver Appraisal Scale [36]. Secondary outcome measures evaluated caregiver well-being via the Center for Epidemiological Studies-Depression Scale [37] and multiple TBI caregiver quality of life [38] subscales assessing feelings of loss, feeling trapped, caregiver anxiety, strain, vigilance, emotional suppression, and family disruption. Secondary outcome measures also evaluated caregiver resource usage, including hospital and residential care service use and community-based services such as housekeeping [39], caregiver personal resources (coping style [40], interpersonal supports [41], and self-efficacy [42]), ADLs/instrumental activities of daily living [43,44], and care recipient behaviors [45].

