### Analysis

Quantitative analysis will include descriptive statistics, such as frequency tables and means, to describe sample characteristics and TBI-AD/ADRD caregiver outcomes. Enrollment and recruitment data, such as the number of contacts or referrals by site, reasons for exclusion, and retention, will be summarized. Distribution/normality and missing data will also be examined.

The number of TBI-AD/ADRD caregivers enrolled to address the study hypotheses (n=80) was determined using power analysis procedures that relied on Wänström’s Monte Carlo simulations [61]. A final sample of 72 TBI-AD/ADRD caregivers was found sufficient for detecting a medium effect size of 0.5 at a statistical power level of 0.8, while adjusting for 10% loss to follow-up and for multiple potential statistical differences between treatment and control groups at baseline. In order to evaluate whether a full-scale randomized controlled design is feasible and appropriate, we will conduct paired *t* tests to determine whether the TACSI treatment and control groups are statistically (*P*>.05) equivalent across all baseline outcomes and TBI-AD/ADRD caregiver covariates. Multilevel regression analyses of outcome and growth curve modeling will be used to compare rates of change between the treatment and control groups in primary subjective stressors and other caregiver outcomes. The primary independent variable will indicate random assignment into the TACSI treatment or control group. If any sample characteristics or outcomes vary significantly at baseline between the treatment and control groups, the baseline values will be included as covariates. In order for the intercept effect to be a main effect and to have a treatment*time interaction effect, the baseline value of each outcome will be a covariate, and time will be centered at 3 months after the baseline survey. We will explore whether treatment participants experienced statistically significant (*P*<.05) declines in primary subjective stress, increased well-being, and other changes in TBI-AD/ADRD caregiver outcomes when compared with controls over the study period. Further, Cox proportional hazard models will be run with the events including admission to a nursing home, assisted living, similar residential living situation, and emergency department and overnight hospital stays.

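### The planned comparison of rates of change covers only months 3 to 6, and neither named model coefficient is the 6-month treatment effect

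*Protocol article*

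**What the plan says.** The Objective in the abstract says that the trial "evaluates the preliminary efficacy and successful implementation of TACSI, a 6-session semistructured psychosocial and psychoeducational program, over a 6-month period". The Analysis section says that multilevel regression and growth curve models "will be used to compare rates of change between the treatment and control groups in primary subjective stressors and other caregiver outcomes". It then fixes the coding, with the stated purpose of obtaining both a main effect of treatment and an interaction with time: "the baseline value of each outcome will be a covariate, and time will be centered at 3 months after the baseline survey". It goes on to promise an exploration of declines in subjective stress relative to controls across the study.

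The Surveys section and Table 1 give three occasions: baseline (T0), T1 ("The first follow-up (T1) was administered at 3 months post completion of the baseline survey") and T2, three months after T1. Table 2 sets the programme as "Six weekly TACSI sessions (approximately 60 minutes each"). The Coaching Sessions overview adds that the weekly rhythm depends on schedules, and the Ad Hoc Sessions section allows further contact after the six sessions.

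The section does not say which coefficient carries the efficacy conclusion, and it names no 6-month contrast.

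**The concern.** The announced comparison and the coding do not match. A reader told that rates of change are compared would take the treatment*time term as the efficacy test over six months. Under the stated coding that term starts at month 3, after six weekly sessions would normally have ended. It measures what happens to the benefit afterwards, not whether there was one.

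The other named term, the treatment main effect, is the difference at month 3. So neither term is the effect at month 6 or over the whole follow-up, which is the horizon the Objective sets. At stake are a misread null on the slope term and a choice between coefficients made after the results are seen, in a pilot meant to inform a full-scale trial.

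**Working it through.** **Inputs from the article.** Final sample 72, allocated 1:1, so 36 per arm; effect size 0.5; significance level 0.05 (two-sided assumed); outcome waves T1 (time 0) and T2 (time 3 months).

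**Assumed, because the article gives no figure.** Equal correlation ρ among the three waves, range 0.5 to 0.7; SD 1 at each wave; normal approximation.

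**The plan's own figure.** 80 × 0.9 = 72, so the dropout allowance reproduces. The stated power of 0.8 cannot be confirmed or refuted, because the inputs to the Monte Carlo procedure are not given. A plain two-mean comparison with 36 per arm gives 0.56. With baseline adjustment, 0.80 needs ρ of about 0.65. The point here does not depend on this.

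**What the coefficients mean.** The model is y = β₀ + β₁·baseline + γ·arm + τ·time + δ·arm·time, with d₁ and d₂ the baseline-adjusted arm differences at T1 and T2.
- At time 0: γ = d₁, the 3-month difference.
- At time 3: γ + 3δ = d₂, so δ = (d₂ − d₁)/3 per month. Nothing before T1 enters δ.
- The 6-month effect is γ + 3δ, a combination of the two coefficients.

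A simulated check (4,000 participants, ρ = 0.6, true difference −0.5 at both visits) gave γ = −0.53, δ = 0.005 per month and γ + 3δ = −0.52.

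**Variances given baseline.** At each visit v = 1 − ρ²; the covariance between visits is c = ρ − ρ². Each contrast has SE = √(variance × 2/36), with variance:
- T1 or T2 difference: v
- d₂ − d₁: 2(v − c) = 2(1 − ρ)
- T1/T2 average: (v + c)/2

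At ρ = 0.6, v = 0.64 and c = 0.24, so the SEs are √(0.64/18) = 0.189, √(0.80/18) = 0.211 and √(0.44/18) = 0.156.

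**Power** is Φ(|d|/SE − 1.96) plus the opposite tail. Examples at ρ = 0.6: T1 term for 0.5 SD, 0.5/0.189 = 2.65, power 0.76; interaction for a change of 0.25 SD, 0.25/0.211 = 1.19, power 0.22; average for 0.5 SD, 0.5/0.156 = 3.20, power 0.89 (0.88 in 4,000 simulated trials).

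| True effect (T1, T2), SD | Main effect (T1) | Treatment*time | T2 difference | T1/T2 average |
|---|---|---|---|---|
| 0.5, 0.5 | 0.69–0.84 | 0.05 | 0.69–0.84 | 0.85–0.94 |
| 0.25, 0.5 | 0.23–0.32 | 0.19–0.28 | 0.69–0.84 | 0.61–0.76 |
| 0.5, 0 | 0.69–0.84 | 0.56–0.78 (shows loss) | 0.05 | 0.32–0.42 |

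Ranges run from ρ = 0.5 to ρ = 0.7.

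**The case against.** The strongest reply is that the centring was deliberate. The sentence that sets it states its purpose: a main effect plus an interaction. The main effect captures benefit gained during the sessions, with fair power, and the interaction then shows whether it grows or fades. Nothing makes the interaction the sole or primary test. The 6-month effect is a routine contrast from the same fit, and an unseen analysis plan may name it. With two follow-up waves, linear time by arm and categorical visit by arm have the same mean structure. The 5% figure needs a benefit complete by T1 and flat afterwards, while sessions may slip and ad hoc support continues. The trial is also a pilot with exploratory language.

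Most of this stands and limits the point. It does not remove the mismatch: the article announces a comparison of rates of change for a 6-month question, and its coding makes the only rate in the model a post-T1 rate. Silence on the deciding contrast would not be a finding on its own; coding that contradicts the announced comparison is.

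Three stronger readings might be inferred, and the document supports none of them:
- *That a fully successful programme would come out null.* This is true of the interaction only; the planned main effect tests the 3-month difference.
- *That the growth model cannot be identified with two waves.* That needs a correlated random intercept and slope, and the article specifies no random effects. A random-intercept model is identified.
- *That the month-3 effect is shrunk because baseline also enters as an outcome row.* The article gives baseline only as a covariate.

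**Conclusion.** The concern holds in a limited form. With baseline as covariate and time zero at 3 months, treatment*time is the T1-to-T2 change only. As a test of rates of change it has power equal to the significance level for a benefit gained by T1 and kept, and it points to loss if the benefit fades. The main effect remains a valid test at 3 months.

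The practical cost is clearest when the effect builds from 0.25 to 0.5 SD: both named coefficients have power 0.19 to 0.32, while the unnamed T2 difference has 0.69 to 0.84. For a sustained effect at ρ = 0.6, the T1/T2 average gains over the T1 term alone (about 0.88 against about 0.75).

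The algebra rests only on the article. The power figures rest on 36 per arm, equal correlations of 0.5 to 0.7 and the effect shapes shown. This should be fixed before outcome analysis; it does not invalidate the design or the data.

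**What to change.** Before outcome analysis begins, revise the Analysis section as follows.
- Keep the baseline score as covariate, with T1 and T2 as the only outcome rows, and model arm by visit.
- Base the efficacy conclusion on one pre-specified baseline-adjusted difference between arms that covers the 6-month aim: either the T2 difference or the T1/T2 average. The choice depends on the question. The average is stronger for a sustained effect, the T2 difference for one that builds.
- Report the T1 and T2 differences, with intervals, whichever is chosen.
- State that the main effect under the present centring is the 3-month difference, and describe treatment*time as maintenance or fading after T1. Remove the description of it as an efficacy comparison of rates of change.

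The cost is a few sentences. No new data are needed and the fitted means are unchanged. The only loss is a single slope summary.

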#### Intervention

##### Coaching Sessions

###### Overview

After randomization, the assigned TACSI coach contacted the caregiver assigned to the treatment group to offer introductory information, including a description of the semistructured program (eg, design, length, and frequency of sessions) and to determine caregiver preferences for participation (eg, modality of delivery).

The TACSI program is a 6-session semistructured psychosocial and psychoeducational program, developed to increase caregiving skills and strategies and provide support to improve mood, reduce stress, and increase caregiver self-efficacy. TACSI provides individual coaching and ad hoc support to caregivers. Intervention sessions are conducted on a weekly basis, as schedules permit. Sessions typically last from 45 minutes to an hour and a half, depending on discussion needs and participant preferences. Sessions are held remotely via telephone or secure video conferencing (ie, Zoom) based on participant requests. Table 2 includes descriptions of TACSI’s mode of delivery, frequency, and other delivery characteristics adapted from the intervention taxonomy of Schulz et al [46].

The initial TACSI session includes an informal interview to build rapport and allow the coach to learn about the caregiver and care recipient, identifying critical stressors and priorities for the intervention. All subsequent sessions include a brief check-in for caregivers to share updates of their previous week and ascertain the most relevant focus of the session, followed by a discussion of pertinent module content. The conclusion of each session may include discussion of self-care plans for the upcoming week, determining goals or homework, and scheduling the next session, if applicable. The order of delivery of TACSI modules 2 through 5 is intentionally flexible to respond to the priorities and needs of the participant. The sixth session serves to discuss any unexplored intervention content, review previously presented material, and address any remaining caregiver questions.

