### Ad Hoc Sessions

Ad hoc sessions, delivered via telephone, secure web conferencing, or email, were available at any time between sessions and following intervention completion. Caregivers could schedule a standing ad hoc session or request impromptu ad hoc coaching. Ad hoc sessions and email consultations were unstructured and designed to address any caregiver concerns in a timely manner.

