#### Bereavement or Residential Placement

If the care recipient passed away during the study, the participating caregiver was offered condolences by the staff. Pending their willingness to continue the study, these caregivers were administered modified bereavement surveys at follow-up. If the caregiver was in the treatment group, they no longer participated in standard TACSI sessions. However, the interventionist offered optional ad hoc sessions focused on the participant’s needs, integrating TACSI content only if relevant. Depending on the number of study time points remaining, either one or two bereavement surveys would be administered, both omitting measures no longer applicable, as shown in Table 1.

In the case of a care recipient’s nursing home admission, the caregiver could continue study involvement (TACSI intervention and routine follow-up surveys) as usual.

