We will calculate means and create frequency tables to evaluate AIM, IAM, and FIM measures and TRC at T1 and T2. We will determine if 80% of treatment caregivers found the intervention appropriate, feasible, and acceptable at the 2 follow-up timepoints (T1 and T2).

Post hoc analyses will also be conducted. Specifically, to examine the effects of TACSI use on changes in primary subjective stress and caregiver well-being, intervention session data regarding variations in use of TACSI, such as frequency and duration of counseling sessions, will also be included in the growth curve models.

The qualitative analysis will use reflexive thematic content analytic techniques as described by Morse, Moser, and others [62-66]. The semistructured interviews and open-ended comments from the TRCs will comprise the qualitative data. The research staff will read the qualitative data to familiarize themselves with the data and make changes to the Phase I codebook accordingly. Staff will review and discuss coding assumptions before making any revisions to the codebook. This qualitative analysis will help determine why TACSI did or did not meet the needs of TBI-AD/ADRD caregivers.

The mixed methods analysis aims to provide empirical context for the participants’ perceptions of TACSI. A sequential mixed methods sampling approach was used in selecting treatment participants for the semistructured interviews. This will enable research staff to better understand participants’ perceptions of TACSI’s usefulness while also linking qualitatively derived themes with the outcome data. Specifically, the empirical outcome data will be sorted by qualitative themes that appeared across the 2 subgroups of the semistructured interview sample (those who rated TACSI as highly acceptable, feasible, and useful in the TRCs vs those who rated TACSI poorly on the same measures). This mixed methods approach will allow us to determine if certain themes appear more often for one subgroup than the other subgroup, or if the subgroups use TACSI recommendations differently.

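### The post hoc session-use models give a confounded association, not an effect of TACSI use, and an arm coefficient from them should not be read as the treatment effect

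*Protocol article*

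**What the plan says.** The main growth models in the Analysis section compare the arms as randomised: "The primary independent variable will indicate random assignment into the TACSI treatment or control group". For adjustment, "the baseline value of each outcome will be a covariate, and time will be centered at 3 months after the baseline survey", and other characteristics that differ at baseline may be added. No session variable appears in these models.

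A later paragraph of the same section begins "Post hoc analyses will also be conducted". Its stated purpose is "to examine the effects of TACSI use on changes in primary subjective stress and caregiver well-being", and to that end session data, "such as frequency and duration of counseling sessions, will also be included in the growth curve models".

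Other sections describe how use comes about:
- **Coaching Sessions, Overview:** "Sessions typically last from 45 minutes to an hour and a half, depending on discussion needs and participant preferences". Sessions are weekly only where schedules allow.
- **Ad Hoc Sessions:** "Caregivers could schedule a standing ad hoc session or request impromptu ad hoc coaching". This contact exists to deal with caregivers' concerns and stays open after the six sessions are finished.
- **Table 2:** caregivers may withdraw from the intervention whenever they wish.
- **Bereavement or Residential Placement:** after the care recipient's death, "If the caregiver was in the treatment group, they no longer participated in standard TACSI sessions".
- **Coach Documentation:** dates and lengths of contact are logged, for control participants as well as treated ones.

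The article does not say whether the arm indicator stays in the use models, how controls are coded, whether only treated caregivers are modelled, or over what period contact is counted.

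**The concern.** The analysis is worded as an estimate of what use does to outcomes, but use was not randomised. A caregiver whose situation worsens may ask for more contact and talk longer. One who is overwhelmed, withdraws or is bereaved may have less. Each of these also bears on stress and well-being. Baseline covariates cannot remove need that arises after baseline.

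Time order is a second problem. Time is centred at 3 months, so the main contrast is the one at T1, while ad hoc contact can continue past T1. A total-use variable would then explain a T1 score partly by contact that followed it.

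Third, TACSI sessions are absent in the control arm. If raw counts are added to a model that also contains arm, the arm coefficient changes meaning.

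At stake is misleading dose evidence carried into the planned larger trial, and a second, incorrect treatment estimate printed beside the correct one.

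**Working it through.** The plan gives no figure for this analysis, so there is nothing of its own to reproduce. The check asks what such a model returns when the truth is known.

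**Inputs from the Protocol article.** Allocation 41 to TACSI and 39 to control (Abstract); effect size 0.5 SD, and baseline outcome as covariate (Analysis).

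**Assumed inputs, not in the documents.** Treated caregivers have on average m = 7 contacts with SD s = 2; controls are coded 0. Unmeasured need arising after baseline raises the stress score by g = 0.5 SD per SD. The correlation between need and contacts is r. The true arm effect is −0.50 SD (negative means benefit), and the number of contacts has no effect at all. The outcome is 0.5 × baseline + 0.5 × need + noise of variance 0.5, plus the arm effect. A linear model at one follow-up stands in for the growth model.

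**Formulas.** With arm in the model and every control at 0, the use slope is identified from variation among treated caregivers:
- use slope = g × r / s = 0.5r / 2 = 0.25r
- arm coefficient = true effect − m × slope = −0.50 − 7 × 0.25r = −0.50 − 1.75r

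**Results**, with means over 4,000 simulated trials of 41 v 39:

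| r | slope, formula | slope, simulated | arm, formula | arm, simulated | slope has P<.05 |
|---|---|---|---|---|---|
| −0.3 | −0.075 | −0.08 | +0.025 | +0.02 | 20% |
| 0 | 0 | 0.00 | −0.50 | −0.51 | 5% |
| +0.3 | +0.075 | +0.08 | −1.025 | −1.02 | 19% |
| +0.5 | +0.125 | +0.13 | −1.375 | −1.37 | 45% |
| +0.7 | +0.175 | +0.18 | −1.725 | −1.72 | 74% |

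**Model without use terms.** The arm coefficient averages −0.50 to −0.51 in every row. Residual variance after baseline is 0.5² + 0.5 = 0.75, so its SE is √(0.75 × (1/41 + 1/39)) = 0.19. With raw counts added, the SE rises to about 0.52.

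**Variations.**
- *No treatment effect, r = +0.5:* the arm coefficient averages −0.90 and has P<.05 in 41% of trials, against a nominal 5%.
- *No confounding (r = 0), whole effect through sessions:* −0.5/7 = −0.07 per contact. The arm coefficient averages −0.01, because it now describes a treated caregiver with no sessions.
- *Use centred within the treated arm:* the arm coefficient returns to about −0.50, but the slopes stay as in the table.
- *Treated caregivers only:* there is no arm coefficient to misread, but the slope is still confounded.

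**The case against.** The strongest reply is that the plan labels this analysis post hoc and keeps it apart from the main comparison. That stands. A reader might infer that the trial's treatment effect will be distorted. The documents do not support this, because the main model rests on random assignment and has no session terms.

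It can also be said that the wrong arm coefficient depends on a coding the article never states. That stands in part. Putting session data into the growth models that compare the arms most plainly means arm and use together. Centring use within the arm, or modelling treated caregivers only, would avoid the shift and is not ruled out. Neither choice removes the confounding of the use slope.

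A reader might infer that the model will make coaching look harmful or exaggerate its benefit. The documents do not fix a direction. Session length depends on preference as well as need, and burdened caregivers may use less; at r = −0.3 the signs reverse. The values near −1.7 need a correlation of 0.7, the highest tried, and are not a forecast.

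A reader might also infer that the choice of essential components would be misled. The Discussion gives that task to the qualitative and mixed methods work, and session counts cannot identify components.

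Finally, coding and time windows may be set out in a fuller document. That is why the point rests on the stated purpose and on the named adjustment, not on missing detail. Calling the analysis post hoc does not change its causal wording, and it is in fact specified before the data are analysed.

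**Conclusion.** The concern holds in limited form. Under any coding, the coefficient for session frequency or duration is a confounded association, possibly biased in either direction, and it can include contact that came after the T1 outcome. It cannot be reported as an effect of use. The randomised comparison itself is sound.

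If arm and raw counts share a model, the arm coefficient is the contrast at zero sessions and not the treatment effect. For a true effect of −0.50 SD it ranges from about +0.02 to −1.37 as the need–use correlation goes from −0.3 to +0.5, with an SE of about 0.52 instead of 0.19. These sizes rest on the assumed distribution of contacts and the assumed link between need and outcome. The change in meaning of the coefficient does not.

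**What to change.** - State that the treatment effect comes only from the growth model without use terms, and that no arm coefficient from a model containing use will be read as the treatment effect.
- Analyse use within the TACSI arm only, labelled exploratory and non-causal, and change the stated aim from effects to association.
- Separate the six planned sessions from ad hoc contact.
- For each outcome survey, count only contact that came before it. The coaches' logged dates and lengths allow this.
- Optionally, if an effect of receipt is wanted, estimate a complier average causal effect with assignment as the instrument. Fix the definition of completion from the session logs before outcomes are seen, and state the exclusion assumption that assignment acts on the outcome only through receipt. This answers a question about receipt, not dose.

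The cost is a few sentences and a simple derivation from existing logs. The use analysis rests on at most 41 caregivers, but in a joint model with arm the slope already came from them, so little information is lost. The plan gives up a causal statement about dose, which these data could not support.
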